### Missing data

Infant weight and height measurements and feeding practices will be missing for participants who are lost to follow-up, who miss study visits and with premature discontinuation from the study. The missing values may depend on observed data and will consider these missing values as missing at random. If there is no correlation between the missing values and the observed data, i.e., Little’s test is not statistically significant (*p* > 0.05), missing values for the outcome variables will be considered missing completely at random. We specify the analysis model, for estimating the intervention effect on stopping breastfeeding, and evaluate how that effect may have changed over the 24-week period and specify maximum likelihood as the method to handle missing data. A multivariate normal model will be specified for the relationships among variables that have missing data. We fit a mixed (random intercept) model with a log link and unstructured covariance matrix or Toeplitz covariance matrix to deal with missing data on repeated measures. Those who drop out contribute records for those time points in which they respond, but not for the later time points. If missing values are missing completely at random or missingness is confined to the outcome variable, we use complete case sensitivity analysis for our primary analyses. Infant growth is estimated and compared between study groups using mixed linear regression models with maximum likelihood estimation for dealing with missing data under the missing at random assumption.

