### Sample size, power, and detectable differences

We expect an exclusive breastfeeding rate of 8% at age 6 months in the usual care group [17]. We want to detect a difference of 15% between the intervention and usual care groups (i.e., 23% vs 8%). The traditional fixed sample size computations using WinPepi give a sample size of 182 for a two-sided test. Using inflation factor 1.01 for two planned analyses of O’Brien-Fleming boundaries at the 0.05 significance level and 80% power, we compute the maximum sample size of 182 × 1.01 = 184. The sample size is inflated by 33% to 275, to account for loss to follow-up (30%) and infants who test HIV positive (3%) who are included in the analysis ignoring infant HIV status and repeat the analysis excluding HIV-infected infants. The study is not powered for the co-primary endpoint (i.e., any form of breastfeeding rate at 6 months of age) and secondary endpoints. The co-primary and secondary endpoint analyses are considered exploratory and may only be supportive of the primary analysis of exclusive breastfeeding endpoint. No adjustment to the significance level for testing of multiple co-primary endpoints is made since all the co-primary endpoint analyses are considered exploratory.

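### The conditions under which the plan turns to complete cases for its primary analyses do not justify them for a two-proportion z-test, and the named maximum likelihood model is not linked to that test

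*Protocol article*

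**What the plan says.** All references are to the protocol article.

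- **Primary efficacy confirmatory analysis.** The one confirmatory test is a group-sequential standard proportion test of exclusive breastfeeding, compared with 1.9776 at the end of the study.
- **Missing data, first condition.** If Little's test gives p > 0.05, "missing values for the outcome variables will be considered missing completely at random".
- **Missing data, second condition and consequence.** Under MCAR, or if "missingness is confined to the outcome variable, we use complete case sensitivity analysis for our primary analyses".
- **Missing data, other method.** The section also says that missingness may depend on observed data, treats it as MAR and names maximum likelihood. For repeated measures it states: "We fit a mixed (random intercept) model with a log link and unstructured covariance matrix or Toeplitz covariance matrix". Dropouts contribute the visits they attended.
- **Sample size, power, and detectable differences.** The section states: "We expect an exclusive breastfeeding rate of 8% at age 6 months in the usual care group". The target is 23% against 8%. The calculations "give a sample size of 182 for a two-sided test"; this becomes 184 for two looks and 275 after a 33% inflation (30% loss, 3% HIV-positive infants).
- **Planned schedule of interim analysis.** The interim z-test is run once 69 participants per group have complete response data.
- **Endpoint variables.** Exclusive breastfeeding means breastmilk only, until 6 months of age. Sample size and Table 2 speak of the rate at 6 months.
- **Mobile phone text messaging and motivational interviewing.** A mother who stops breastfeeding completely is taken to have reached the co-primary outcomes.

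**The concern.** The rule that leads to complete cases rests on two conditions, and neither does what the plan needs.

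First, failing to reject MCAR is not evidence for MCAR, especially with about 275 pairs. Second, missingness confined to the outcome is harmless only when loss is unrelated to the outcome given everything the analysis conditions on. A raw z-test conditions on arm and nothing else. It ignores feeding at weeks 2, 6 and 10, which is likely to predict both loss and the week-24 result. The z-test's only variables are arm, always known, and feeding status, so for that test the second condition is met whenever anything is missing.

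Differential loss is plausible from the text. Mothers know their arm, text messages stop for intervention mothers who stop breastfeeding completely, and the Safety events section lists guilt over not breastfeeding exclusively. With a 30% loss allowance and an expected 8% event rate in usual care, how the lost pairs are handled could affect the trial's conclusion.

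**Working it through.** **1. The plan's own figures.** For 8% against 23%, two-sided 0.05 and 80% power without continuity correction, the two-proportion formula gives 91 per arm, or 182. Then 182 × 1.01 = 183.8, so 184, and 184 / (1 − 0.33) = 274.6, so 275. All three reproduce. The 275 is the enrolment that leaves 184 analysable pairs, which is the logic of a complete-case test. At the final look alone, 1.9776 has two-sided error 2 × 0.0240 = 4.8%.

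**2. Which method feeds the z-test?** The z-test has no likelihood step for a missing outcome. The log-link mixed model is not said to produce the z-statistic. The sizing and the interim wording fit complete cases. The sections have not been reconciled.

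**3. Does a non-significant Little's test show MCAR?** This was simulated with 300 trials per pattern. Assumed exclusive rates at weeks 2, 6, 10 and 24 were 75/50/33/8% in usual care and 82/62/48/23% in intervention, with total loss of about 27–30%. The share of trials with p > 0.05 was:

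| Dropout mechanism (assumed) | Non-significant |
|---|---|
| MCAR | 96% |
| Depends mildly on last feeding status | 76% |
| Depends more strongly on last feeding status | 38% |
| Depends on unseen current status, moderate | 75% |
| Depends on unseen current status, strong | 33% |

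The test often passes data that are not MCAR.

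**4. Complete-case bias with no true effect.** Assumptions: 40% exclusive at week 10 and 8% at week 24 in both arms, and loss depending on week-10 status. The complete-case rate is P(exclusive at week 24) × (1 − loss if exclusive) / P(observed).

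- Usual care, 30% random loss: 0.08 × 0.70 / 0.70 = 8.0%.
- Intervention, loss 15% if exclusive and 40% if stopped: total loss is 0.4 × 0.15 + 0.6 × 0.40 = 30%, so the rate is 0.08 × 0.85 / 0.70 = 9.7%.
- Difference +1.7 points, although both arms lose exactly 30%.
- Simulated error at 1.9776 (138 and 137 per arm): upper tail 5.9%, lower tail 0.8%, two-sided about 6.7%, against 4.8% nominal (upper tail 2.4%).
- With 10%/45% loss in the intervention arm the upper tail is 8.0%.
- With 15%/40% loss in both arms, two-sided error stays at about 4.8%.

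**5. Complete-case bias with a true 15-point effect.** Under random loss the estimate is unbiased, with power of 82% on complete cases against 93% if all 275 are observed. In the extreme case where only failures are lost, 30% of each arm, the rates become 0.08 / 0.70 = 11.4% and 0.23 / 0.70 = 32.9%, a difference of 21.4 points. If 45% of usual-care failures and 20% of intervention failures are lost, the rates are 0.08 / (0.08 + 0.92 × 0.55) = 13.7% and 0.23 / (0.23 + 0.77 × 0.80) = 27.2%. The difference is 13.5 points and power is 62%.

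**6. Earlier feeding reports.** If the endpoint is exclusivity until 6 months, other feeds reported at week 2, 6 or 10 settle it. In the step 3 simulation, about 45–60% of usual-care dropouts had already been seen to fail. Keeping those and dropping the other lost pairs is not a clean repair. With 30% random loss and every lost failure known, the rates are 0.056 / 0.976 = 5.7% and 0.161 / 0.931 = 17.3%, so 15 points shrink to 11.6. With half known, they shrink to 13.1. Unresolved pairs must be modelled, not dropped.

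**The case against.** A reader might infer that the protocol declares a complete-case primary test. It does not. The words are complete case sensitivity analysis, MAR is the starting assumption, and maximum likelihood is the named method. This stands: complete-case handling of the z-test is inferred from the test, the sizing and the interim wording. The two conditions are nevertheless stated rules rather than omissions, so they cannot be left to an unseen SAP.

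A reader might also infer that known failures are thrown away. No section says so, and the rule on complete stoppers suggests that they keep their result. What remains is the mother who adds other feeds and is then lost: no section keeps her. Even that depends on reading the endpoint as until, not at, 6 months, and feeding is measured by recall of the last week or 24 hours.

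A further tempting point is that "A multivariate normal model will be specified for the relationships among variables that have missing data", and that a Toeplitz matrix suits unequal visit gaps badly. This fails. The section's missing variables include infant weight and height, so the normal model is not tied to binary feeding status, and unstructured covariance is offered as the alternative to Toeplitz.

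Three more objections stand in part. Gaps in viral load or CD4 count could defeat the outcome-only condition in the adjusted models, though not in the z-test. Telephone interviews and home visits may keep the actual loss below 30%. The document gives only 8%, 23% and 30%, so every loss pattern above is an assumption.

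**Conclusion.** The point holds in a limited form. Neither a non-significant Little's test nor outcome-only missingness justifies complete cases for a z-test that conditions on arm alone, and the plan does not say how its maximum likelihood model reaches that test or its boundary. The documents do not support saying that the trial's error rate is inflated. Random loss gives no bias, and equal outcome-related loss in both arms leaves type I error nominal, although the estimated size of a true effect can still shift. When loss depends on feeding in one arm only, the assumed pattern gives about +1.7 points and a two-sided error of about 6.7% against 4.8%. That is moderate, and equal overall attrition would not reveal it. The matter should be settled before any unblinded efficacy analysis.

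**What to change.** 1. Delete the Little's-test and outcome-only conditions from Missing data.
2. State one primary estimator on all randomised pairs, under MAR, that uses feeding at weeks 2, 6 and 10. One option is multiple imputation within arm by logistic models on earlier feeding and baseline covariates, with the pooled z compared with 1.9776. Say how the interim test is handled in the same way.
3. Align the until-6-months definition in Endpoint variables with the at-6-months wording in Sample size and Table 2. If until is kept, count an earlier recorded failure as not exclusive, including mixed feeders later lost, and impute the unresolved pairs.
4. Keep complete cases as a sensitivity analysis and add a delta analysis by arm.

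The cost is protocol or SAP wording and modest programming, with no new data or participants. The downside is that the primary estimate then rests on an explicit MAR model for the unresolved pairs, which the delta analysis is there to test.

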### Planned schedule of interim analysis

One interim analysis meeting is held to review data on intervention efficacy and safety. The Data Safety Monitoring Board (DSMB) assess between groups (intervention vs usual care): (i) preliminary assessments of efficacy (i.e., exclusive breastfeeding rate) and ii) co-primary endpoint, any form of breastfeeding rate and secondary endpoints.

Interim analysis is performed after 69 participants per group have complete response data. A group-sequential test using the O’Brien-Fleming boundaries rejects the null hypothesis of no difference in exclusive breastfeeding rate between the intervention and usual care groups, at the interim analysis if the computed z-statistic exceeds the O’Brien-Fleming boundary value of 2.7967. The DSMB determine whether this predefined trial efficacy stopping rule is met.

### Stopping rules

The DSMB members determine whether predefined trial efficacy stopping rules is met, the DSMB makes a recommendation to the study team to continue or to terminate the trial.

### Monitoring

#### Data monitoring

The trial steering group meets bi-monthly reviewing trial conduct and progress. The DSMB has six voting members with expertise in HIV and infant feeding, epidemiology, and randomized clinical trials. The DSMB membership is restricted to individuals without significant conflicts of interest who independently oversee and evaluate the efficacy of the interventions, safety, study conduct, and scientific validity and data integrity of the study at yearly intervals and ad hoc, if necessary, until the last participant completes the study. The DSMB provides a recommendation to investigators, whether the study should continue unchanged, be stopped due to adverse effects or efficacy, or be modified in any way.

### Trial safety monitoring

The DSMB reviews the unblinded safety data accruing in the study, including an assessment of relatedness to trial intervention. Adverse events or unanticipated problems involving risks to participants are reported to DSMB, EDCTP project officer, and ethics committee within seven working days of the event, including a description of the measures taken in response to the event (if any). The DSMB can suspend the trial for safety concerns even if no formal holding rule has been predefined and recommend appropriate action.

### Procedure if the trial is put on hold

If the trial is put on hold because of a safety concern, enrolment in the trial and all interventions cease immediately, but safety procedures continue. The DSMB reviews all available safety data and makes a recommendation to the study team whether the trial should be stopped permanently, modified, or continue unchanged.

### Quality assurance of statistical programming

At the end of the trial, the study team will independently conduct the primary analyses and inform the DSMB, to ensure concordance between what the DSMB has reviewed during study monitoring. The study team review the entire analyses and check the programming code used by the data analyst.

### Ethical considerations

Stellenbosch University Human Research Ethics Committee (reference M21/03/010) approved the study. Western Cape Department of Health approved access to Khayelitsha District Hospital for study recruitment (reference WC_202107_007). Study participation is voluntary, mothers have the right to withdraw their participation at any time. Mothers undergo an informed consent process with a research assistant, in their native language Xhosa or English and sign a written informed consent document for their and their child’s participation in this study. In the unlikely event of the participant sustaining physical injury through study participation, the participant is insured by Stellenbosch University’s research policy.

Mothers have the option to consent or decline to their and their child’s anonymized and de-identified data being contributed to SUNScholarData and pooled with other maternal-child studies with appropriate institutional review board approvals for any additional pooled analyses. As children are enrolled and followed to age 6 months, no assent is feasible. The ethics committee have access to source data documents for monitoring purposes. A progress report is submitted annually, for renewal of ethics approval by the Stellenbosch University Human Research Ethics Committee. The data analyst has access to the anonymized final dataset. The trial was registered on ClinicalTrials.gov (NCT05063240) and Pan African Clinical Trial Registries (PACTR202110870407786) before the recruitment of the first subject.

## Discussion

Our study complements other work done in our setting and is aligned with the South African national and provincial sustainable development priorities. The work presents an opportunity to determine whether text messaging and motivational interviewing sustain breastfeeding and improve infant health outcomes. Thus, this project contributes towards achieving the Sustainable Development Goal 3 call for an end to preventable deaths of children under 5 years. Findings from this study may facilitate decision-making on (1) whether implementation of the breastfeeding policy achieved the desired outcomes, (2) interventions needed to sustain breastfeeding among women living with HIV, and (3) whether the interventions do have an impact on child health and survival. Should we find no effect of text messaging and motivational interviewing on sustaining breastfeeding and improving child health, the study can still inform decision-making regarding breastfeeding policy. Should we find the intervention effective, we will, in collaboration with the Western Cape Provincial Vertical Transmission Prevention of HIV strategic programme adapt the health services practices to provide the necessary support to sustain breastfeeding for longer.

## Trial status

Protocol version number 1 31 May 2021, recruitment began on 22 July 2023, and the approximate date recruitment is expected to be completed is 31 October 2023.

## Data Availability

The data will be deposited into the SUNScholarData, a data repository that is managed by the Stellenbosch University Library. Mothers have the option to consent or decline to their and their child’s anonymized and de-identified data being contributed to SUNScholarData and pooled with other maternal-child studies with appropriate institutional review board approvals for any additional pooled analyses.

## Abbreviations

cART: Combination antiretroviral treatment
DSMB: Data Safety Monitoring Board
EDCTP: European & Developing Countries Clinical Trials Partnership
HEU: HIV-exposed uninfected
HIV: Human immunodeficiency virus
NHLS: National Health Laboratory System
PI: Principal investigator
REDCap: Research Electronic Data Capture
